ISAC APPLICATION FORM:

PROTOCOLS FOR RESEARCH USING THE GPRD DATA

| ISAC use only:  Protocol Number  Date submitted | Team 2  10_152  26/10/2010 | **IMPORTANT**  **If you have any queries, please contact ISAC Secretariat: ISAC**[[name]](mailto:[contact]) |
| --- | --- | --- |

| 1. Study Title        Risk of breast cancer in users of exogenous female hormones |
| --- |

| 1. Does this protocol describe a purely observational study using GPRD data (this may include the review of anonymised free text)?   Yes xNo |
| --- |

| 1. Does this protocol also seek access to data held under the GPRD Data Linkage Scheme?   Yes No x |
| --- |
| 1. If you are seeking access to data held under the GPRD Data Linkage Scheme, please select the source/s of linked data being requested.   Hospital Episode Statistic^†^  Cancer Registry Data *  MINAP*  Townsend Score  ONS Mortality Data  Other: *(please specify)*  ** Please note that access to these data sources are not covered under the GPRD-MRC Scheme.*  ^†^ *Please note that only limited access to this data source is covered under the GPRD-MRC Scheme.* |
| 1. If you are seeking access to data held under the GPRD Data Linkage Scheme, have you discussed your request   with a member of the Research team?  Yes  No  If *No*, please contact the GPRD Research Team to discuss your requirements before submitting your application. |

| 1. Does this protocol involve requesting any additional information from GPs?   Yes No x  If yes, please indicate what will be required:    Completion of questionnaires by the GP* Yes No  Provision of anonymised records (e.g. hospital discharge summaries) Yes No  Other (please describe)  *any questionnaire for completion by GPs needs to be approved by ISAC before being sent out for completion. |
| --- |

**GUIDANCE ON ANSWERING QUESTIONS 4-6:**

**These questions must be completed by all applicants. You should note the following:**

**(i) If you have answered NO to question 2, may need to seek separate ethics approval from an NHS Research Ethics Committee for this study. The ISAC will provide advice on whether this may be needed.**

**(ii) If you have answered YES answered to question 2 above and you will be using data obtained from the GPRD Group at the MHRA, this study does not require separate ethics approval from an NHS Research Ethics Committee.**

**If you will be using data obtained from EPIC, you will need to consult the data provider regarding their arrangements for obtaining ethics approval for the study.**

**NB:** Answering YES to question 2 means that the answers to questions 7-9 should all be NO. If any of the answers below are YES please review your answer to question 2 as it should be NO.

| 1. Has this protocol been peer reviewed by another Committee? Yes No x   *If yes, please state in your protocol the name of the reviewing Committee/s and provide an outline of the*  *review process and outcome on final review.* |
| --- |

| 1. Does the study involve linking to patient *identifiable* data from other sources? Yes No x |
| --- |

| 1. Does this study require contact with patients in order for them to   complete a questionnaire? Yes No x |
| --- |

| 1. Does this study require contact with patients in order to collect a sample? Yes No x   If yes, please state what will be collected |
| --- |

| 1. Type of Study *(please tick one box below)*   Adverse Drug Reaction Drug Use Disease Epidemiology xPharmacoeconomic Drug Effectiveness  Other |
| --- |

| 1. Data source *(please tick one box below)*   GPRD Division at MHRA Other  *(please specify)*  Full Feature on-line access  Ad hoc dataset  MRC dataset  *x*  Other commissioned study |
| --- |

| --- |

**Protocol content checklist**

In order to help ensure that protocols submitted for review contain adequate information for protocol evaluation, ISAC have produced instructions on the content of protocols for research using GPRD data. These instructions are available on the GPRD website ([www.gprd.com/ISAC](http://www.gprd.com/ISAC)). All protocols using GPRD data which are submitted for review by ISAC must contain information on the areas detailed in the instructions. IF you do not feel that a specific area required by ISAC is relevant for your protocol, you will need to justify this decision to ISAC.

Applicants must complete the checklist below to confirm that the protocol being submitted includes all the areas required by ISAC, or to provide justification where a required area is not considered to be relevant for a specific protocol. Protocols will not be circulated to ISAC for review until the checklist has been completed by the applicant.

**Please note, your protocol will be returned to you if you do not complete this checklist, or if you answer ‘no’ and fail to include justification for the omission of any required area.**

|  | **Included in protocol?** | |  |
| --- | --- | --- | --- |
| **Required area** | **Yes** | **No** | **If no, reason for omission** |
| ***Lay Summary (max.200 words)*** | **x** |  |  |
| ***Objective, specific aims and rationale*** | **x** |  |  |
| ***Background*** | **x** |  |  |
| ***Study Type***  *Hypothesis Generating*  *Hypothesis Testing* | **x** |  |  |
| ***Study Design Methodology*** | **x** |  |  |
| ***Study population, including estimate of expected number of relevant patients in the GPRD*** | **x** |  |  |
| ***Sample size/ power calculation*** | **x** |  | *Please provide detailed justification of sample size in the protocol* |
| ***Selection of comparison group(s) or controls*** | **x** |  |  |
| ***Exposures, outcomes and covariates*** | **x** |  |  |
| ***Data/ Statistical Analysis***  *Hypothesis Generating*  *Hypothesis Testing* | **x** |  |  |
| ***Patient/ user group involvement ^†^*** |  | **x** | **not necessary for this analysis** |
| ***Limitations of the study design, data sources and analytic methods*** | **x** |  |  |
| ***Plans for disseminating and communicating study results*** | **x** |  |  |

Breast cancer is strongly influenced by female sex hormones such as oestrogen and progesterone; both by those produced naturally in a woman's body (endogenous hormones), and by hormones taken for contraception or as hormone therapy for the menopause (HT) (exogenous hormones). Current users of both hormonal contraceptives and HT have an increased risk of breast cancer, up to 2-fold in the case of HT preparations containing both oestrogen and a progestagen (synthetic progesterone). Understanding these risks has direct implications for public health: for example, rates of breast cancer have fallen in response to falls in prescribing of HT, following publication of reliable evidence on breast cancer risk in recent years. There are however some gaps in our knowledge. It has been suggested that the effect of HT on breast cancer risk may depend on the timing of use (in relation to age or menopausal status); and there is limited information on the risks associated with progestagen-only contraceptives, or with specific contraceptive formulations. The GPRD's large size and the availability of detailed prescription data by type will allow us to examine these questions; our analyses would extend and supplement previous GPRD studies of hormone use and breast cancer.

Objectives, specific aims and rationale

*Research objective:* to obtain relative risks for incident breast cancer in relation to prior prescribing of contraceptive hormones and of hormone replacement therapy for the menopause (HT), by type and timing of use.

*Specific aims:* to add to existing knowledge about the effect of use of exogenous female sex hormones on risk of breast cancer, examining unanswered questions including the influence on risk of the timing of HT use, and suggested differences in risk associated with specific contraceptive preparations.

*Rationale:* current use of both HT and contraceptive hormones has been shown to increase risk of breast cancer, and this knowledge has direct public health implications. The large size and reliable prescribing information in the GPRD will allow us to add to existing knowledge by examining breast cancer risk in relation to specific hormone preparations and to timing of HT use, where there is at present suggestive but unconfirmed evidence for differences in risk.

Background

The development of breast cancer in women is strongly influenced by female sex hormones, and the risks associated with reproductive patterns (parity, age at first birth) and with use of oral contraceptives and of hormone therapy for the menopause have been extensively described [1-6]. However, unanswered questions remain. For hormonal contraceptives, there is good evidence for a modest increase in risk of breast cancer in current users of oral contraceptives containing both oestrogen and progestagen, both for older [4] and more recent [7] preparations, with relative risks for current compared with never use of around 1.3. There may be higher risks associated with specific formulations and modes of delivery, such as triphasic pills containing levonorgestrel [7], but evidence is limited. Similarly the risks associated with use of progestagen-only contraceptives, including the intra-uterine device Mirena, are not clear [4].

Some types at least of hormone therapy for the menopause are known to be associated with increased risk of breast cancer, with relative risks of about 2 reported for current use of combined oestrogen-progestagen preparations [8]. It has recently been suggested that the effect of HT use on breast cancer risk may vary depending on women's age and/or menopausal status when use starts, with risk higher for use starting around the time of the menopause than for later use [9]. Such findings have important potential implications for clinical practice and need to be investigated in independent datasets. There is debate too about the relative risks associated with different formulations of HT, including, again, the use of Mirena progestagen-releasing intrauterine devices [10]; as well as differences by mode of drug delivery (transdermal vs oral) [11].

We are not aware of previous research studies in the GPRD examining cancer risk in relation to use of hormonal contraceptives. For HT, five previous publications have described analyses of HT use and risk of breast cancer from the GPRD [12-15]. The most comprehensive, with 6,347 cases aged 50-75 [14], used data up to 2004; the most recent (1261 cases with data to 2007) focussed on risk associated with a specific progestagen, dydrogesterone [15]. Our proposal would allow updating and extension of the previous analyses to 2010, to include all HT types, including Mirena, and to examine risk by timing of use.

Reliable analyses by hormone type require large numbers of exposed cases, as well as detailed prospective information on prescribing. The GPRD has both, and sufficient information to allow adjustment or stratification by known potential confounders such as body mass index and alcohol use (as well as some less well-established risk factors for breast cancer such as smoking and use of aspirin).

Finally, a major source of evidence on the effects of exogenous sex hormones on breast cancer risk has been, and will continue to be, the results from pooled reanalyses of individual data included in the international Collaborative Group on Hormonal Factors in Breast Cancer mentioned above. The proposers of the current study also run this collaboration; collaborative results are currently being updated for both hormonal contraceptives and for hormone therapy for the menopause, and a comprehensive and up to date analysis of GPRD data would allow the optimal contribution from GPRD to the worldwide evidence.

Study type

Hypothesis testing and confirmation of findings of public health significance.

Study design

Nested case-control study within defined cohort in GPRD, using cases and controls matched for age, practice and observation time in the GPRD. 2 controls will be selected per case to maximise study power.

Study population

Women aged 20-79 years registered with GPRD on or after 1 January 1995.

Inclusion criteria:

- Age 20-79 [age group includes almost all cancers and hormone prescriptions]
- Registered with GPRD up –to-standard practice on or after 1 January 1995
- Fulfilling GPRD acceptable patient criteria
- At least 1 year in GPRD before index date (date of diagnosis of case)

Exclusion criteria:

- Previous invasive or *in situ* breast cancer

Case selection

Cases will be identified as any eligible patient with an incident diagnosis of invasive or *in situ* cancer of the breast between 1 January 1995 and latest available date.

Selection of comparison group (controls)

2 controls per case selected from eligible patients who do not have a medical diagnosis of breast cancer documented at any time up to the latest available date (above). This includes diagnoses of breast cancer prior to or during the study period. Controls and cases matched on age (within 2 years), practice and observation time in GPRD (ie controls to have observation time in GPRD at least as long as their matched case, to allow exact matching in the analysis; for cases, start date of observation = most recent of patient registration date, practice up-to-standard date and practice management start date, end date (index date) = date of diagnosis). Index date for controls defined as the diagnosis date of their matched case.

Sample size and power calculations

Incidence of invasive breast cancer in GPRD is similar to that in the general UK population, which is ~63 per 100,000 per year (Office for National Statistics (ONS), 2007) ie 630 cases per million person years. There are currently 62 million person years of research acceptable followup in GPRD (GPRD Gold October 2010 release), so we might expect some 39,000 incident breast cancers in the whole database, and of these about 20,000 will be in women aged 50-75 (ONS, 2007). It seems reasonable to assume, allowing for some restriction of age group and observation time, that our analyses would include at least 10,000 breast cancer cases and 40,000 controls. These numbers are consistent with those in the GPRD study by Opatrny et al, which included incident cases of invasive breast cancer in women aged 50-75 diagnosed between 1998 and 2004, and had over 6,000 cases [14]. From the Opatrny study and from our previous analyses in GPRD (protocol no. 10_006; analyses not yet published) the prevalence of HT prescribing in women over 40 years will be approximately 33 % (possibly lower in very recent years); OC prescribing in women 20-50 years is estimated at about 20 % in GPRD in recent studies of outcomes other than cancer [16].

With these numbers the study will be amply powered with 80% power and 95% confidence to detect a minimum relative risk of <1.1 in relation to overall risk for HT or OC use v no use, and of <=1.5 for any subgroup with exposure prevalence of 1% or more.

Exposures, outcomes, covariates

Exposure: patients will be considered exposed to exogenous hormones if they have at least one prescription for a hormonal contraceptive or hormone replacement therapy preparation (as defined in the British National Formulary (BNF)) within the observation period (start of follow-up to index date). Sensitivity analyses will be performed restricting the definition of exposure to those with 2 or more prescriptions. OC/HT type will be assigned based on BNF classification, classing women with separate prescriptions on the same day for oestrogen and progestagen as being prescribed combined oestrogen-progestagen therapy.

Outcomes: incident invasive and *in situ* cancers of the breast (ICD-10 C50 and D05)

Covariates: smoking status, alcohol drinking [most recent record before index date], body mass index [most recent record at least 2 years before index date, to account for reverse causality] and parity will be taken into account where possible in adjusted and/or stratified analyses. Availability of prescription data will allow medications such as aspirin and bisphosphonates, which may be related to breast cancer risk and to hormone use, to be considered in supplementary analyses.

Data/statistical analysis outline methodology

Conditional logistic regression will be used to estimate crude and adjusted odds ratios (relative risks) with 95% confidence intervals for cancer risk in relation to hormone prescription vs no prescription within the observation period. Analyses for hormonal contraceptives will include hormone type and mode of delivery, including progestagen-only contraception; for HT, hormone type, mode of delivery and timing of use; for both, the risks associated with use of Mirena will be examined. Adjustment variables will include smoking status (never, current, past, unknown), alcohol drinking (none, some, unknown) and body mass index (<25, 25-30, 30+ kg/m sq, unknown) and where possible, parity (at least nulliparous, parous, unknown). Data analysis will be carried out using STATA software v10. Analyses for HT will generally be restricted to women aged over 40, and for OC use to women aged 20-50 years.

Patient/user group involvement

None

Limitations of study design, data sources, analytic methods

Validation studies have shown GPRD outcome and exposure (prescription) data to be sufficiently reliable and complete for epidemiological analysis; and the GPRD population is sufficiently representative of the UK population for the results to be broadly generalisable.

Potential limitations of the GPRD for these analyses include the lack of complete information on smoking, alcohol and body mass index, and particularly on reproductive factors such as parity, breastfeeding history and age at first birth; and the fact that information on prescribing of hormonal contraceptives is likely to be incomplete, as prescriptions issued outside general practice will not always be recorded. It is estimated that 80% of all prescriptions for hormonal contraceptives in the UK are issued in general practice (UK Family Planning Organisation, personal communication). Data on other potential confounders, such as diet and socioeconomic status, are not available (the impact of the latter will to some extent be minimised by matching of cases and controls by GP practice).

Such missing data will have the effect of diluting the study power, but should not introduce bias unless data is missing for reasons related to the outcome. The consistency of the results of previous HT studies in GPRD with those from studies in which reproductive factors were taken into account argues against substantial bias in the database; similar comparisons will help in interpreting results on hormonal contraceptive use. Sensitivity analyses with restriction to patients with full data on adjustment variables (complete case analysis) will be performed to test the effect of missing data in the main analyses.

Use of other prescribed drugs which may affect breast cancer risk (eg bisphosphonates, NSAIDs) cannot readily be taken into account by adjustment as there are complex possible relationships between prescribing of these drugs and of HT. Stratified analyses will allow these factors to be taken into account to some extent.

Plans for communicating and disseminating results

We aim to publish the results of this study in a peer-reviewed journal at the earliest opportunity. Study results will also be submitted for presentation at an appropriate scientific meeting. There are no restrictions on the extent or timing of publication.

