**Revised definitions of cases and controls**

In keeping with the above protocol, the revised definitions for cases and controls are outlined as follows. All women are required to have a minimum of 12 months up-to-standard data in the CPRD prior to index date (date of diagnosis for the case) to be eligible for study inclusion.

Case definition

Cases are defined as all female participants of the CPRD with incident diagnosis of invasive or in situ breast cancer documented between 1^st^ January 1995 and 2017 (to most recent data available), and aged 20- 79 years of age at index diagnosis. Women are excluded if they have a past history of invasive or in situ breast cancer.

The list of Read codes used to flag women with incident breast cancer diagnosis as per previous protocol is shown Appendix 1.

Control definition

Controls are defined as all women without a medical diagnosis of breast cancer documented (up to last date of data extraction for 2017). This includes any diagnoses for breast cancer prior to 1^st^ Jan 1995 and during the study period from 1^st^ Jan 1995 to 2017. Cases are therefore not eligible to act as controls in this study.

Controls will be matched in a 2:1 ratio to cases based on:

- Year of birth(+/- 2 years)
- Same general practice
- Similar period of observation as the case.

The period of observation in CPRD for controls must include the full observation time (regstart to index diagnosis) for cases, so that observation periods may be matched exactly for the purpose of analyses.

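### Controls must have no breast cancer recorded up to the end of the data, so they are selected on events after their index date and the odds ratios slightly overstate harmful relative risks.

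*Protocol*

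**What the plan says.** The Study design section of the protocol declares a "Nested case-control study within defined cohort in GPRD, using cases and controls matched for age, practice and observation time in the GPRD".

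Under Selection of comparison group (controls), controls come from eligible patients "who do not have a medical diagnosis of breast cancer documented at any time up to the latest available date". The next sentence spells out the reach of the rule: "This includes diagnoses of breast cancer prior to or during the study period". The same section fixes the reference date: "Index date for controls defined as the diagnosis date of their matched case".

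The amendment of September 2017 keeps the rule, moves its end to the last 2017 extraction, and concludes under Control definition: "Cases are therefore not eligible to act as controls in this study".

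The Data/statistical analysis outline methodology section then states: "Conditional logistic regression will be used to estimate crude and adjusted odds ratios (relative risks) with 95% confidence intervals". The limitations section does not mention the way controls are selected, and none of the stated sensitivity analyses addresses it.

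**The concern.** In a nested case-control study, the controls for a case should be a sample of the women still at risk on that case's index date. That includes women who become cases later. The matched odds ratio then estimates the rate ratio without a rare-disease assumption.

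Here eligibility depends on what happens after the index date. A woman observed and cancer-free in 1996 but diagnosed in 2005 meets the cohort criteria in 1996, yet she cannot be a control for a 1996 case. If the exposure raises risk, such women are more often exposed than the rest. Removing them lowers the exposure odds among controls and raises the odds ratio. A larger sample does not reduce this.

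At stake is the accuracy of the effect estimates that are reported as relative risks and are intended for a worldwide pooled reanalysis. The false-positive rate is not affected.

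**Working it through.** **The plan's own figures.** Expected cases: 62 million person-years × 630 per million = 39,060, against a stated 39,000 or so. For the power statement, take case exposure p1 = OR·p0/(1 + p0(OR − 1)), two-sided 0.05 and 80% power. With 10,000 cases and 40,000 controls, the minimum detectable odds ratio is 1.068 at 33% exposure, 1.080 at 20% and 1.335 at 1%. At the planned two controls per case it is 1.075, 1.088 and 1.372. All satisfy the stated limits of below 1.1 overall and at most 1.5 for a subgroup with 1% exposure.

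**Inputs for the bias**
- From the Background: relative risks (RR) of about 1.3 for current oral contraceptive use and about 2 for current combined HT.
- From the sample size section: exposure prevalence p of 20% (OC) and 33% (any HT).
- Incidence λ: the documents give 63 per 100,000 per year overall. For women aged 50-75 they give 20,000 cases but no person-years. If those women supply 10%, 14% or 20% of the 62 million (assumption), the rate is 323, 230 or 161 per 100,000. The range used is 63 to 350.
- Look-ahead T, from index date to end of data: up to 16 years for 1995-2010 and up to 23 for 1995-2017.
- Assumptions: index dates spread evenly over the window; 0% or 8% of women leaving the database per year; exposure effect constant over the look-ahead.

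**Formula.** The rate in unexposed women is λ0 = λ/(1 − p + p·RR). Dropping later cases multiplies the control exposure odds by S1(T)/S0(T), so for a fixed T

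OR = RR × exp[(RR − 1)·λ0·T].

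Averaged over T, OR = RR × mean(e^(−λ0·T)) / mean(e^(−RR·λ0·T)).

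**Averaged over index dates**

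| Window | Leaving per year | Rate per 100,000 | True 1.3 becomes | True 2 becomes |
|---|---|---|---|---|
| 16 y | 8% | 63 | 1.301 | 2.005 |
| 16 y | none | 230 | 1.307 | 2.028 |
| 23 y | 8% | 230 | 1.306 | 2.023 |
| 23 y | none | 230 | 1.310 | 2.040 |
| 23 y | none | 350 | 1.315 | 2.061 |

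This is +0.1% to +1.1% at RR 1.3 and +0.3% to +3.0% at RR 2.

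**Worst case** (index date at the start of 1995, full 23 years, 350 per 100,000):
- RR 2: λ0 = 350/1.33 = 263 per 100,000; exp(0.00263 × 23) = 1.062, so OR = 2.125 (+6.2%).
- RR 1.3: λ0 = 350/1.06 = 330 per 100,000; exp(0.3 × 0.00330 × 23) = 1.023, so OR = 1.330 (+2.3%).

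**Direction.** At RR 1 the exponent is zero and there is no bias. At RR 0.8 the odds ratio falls to 0.786-0.800, so the shift is away from 1 on either side.

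**Sensitivity to p.** Prevalence enters only through λ0. A rarer exposure with RR 2 can raise λ0 to at most λ. At 350 per 100,000 over 23 years, the average factor is then [(1 − e^(−0.0805))/0.0805] / [(1 − e^(−0.161))/0.161] = 0.9608/0.9237 = 1.040, so +4.0% instead of +3.0%. The worst case becomes exp(0.0805) = 1.084.

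**Simulation.** Matched 1:2 sets were drawn with and without later cases among the controls. At RR 2, 350 per 100,000 and 23 years, the rule gave 2.053 against 1.984 with risk-set controls (standard error 0.0075 on each log odds ratio), a clear difference. At RR 1.3, 230 per 100,000 and 23 years it gave 1.309 against 1.293 (standard error 0.0106), in the expected direction but within noise. Two runs at RR 2, 230 per 100,000 and 16 years could not be separated from sampling error.

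**The case against.** The strongest reply is that the effect is too small to matter. Reading 1.30 as 1.31, or 2.00 as 2.04, changes no conclusion. The formula also leans high. It keeps the full relative risk for the whole look-ahead, while the cited risks are for current use; depletion of exposed controls is weaker if users stop and the excess fades, or if unexposed women start later. The rule is explicit and the same in both versions, so the author's intention is not in doubt. All of this stands, and it sets the severity.

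Three stronger readings are tempting and are not supported.

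- **That the bias is as large as the random error.** With 33,000 cases, two controls each and 33% exposure, the standard error of the log odds ratio is √(1.5/(33,000 × 0.33 × 0.67)) = 0.0143, a 95% half-width of about 2.8%, close to the 3.0% above. But the 33% is any HT prescribing in women over 40, the relative risk of 2 is for current combined HT, and the 33,000 cases cover ages 20-79 while HT analyses are generally limited to over 40. At RR 2 with all 33,000 cases, the half-width is 3.9% at 10% exposure, 5.2% at 5% and 11.5% at 1% (assumed prevalences, unmatched variance). For OC at 20% and RR 1.3 it is 3.2%, about three times the largest average bias of 1.1%.
- **That the rule creates an artificial calendar trend in the results.** The bias does grow with look-ahead, but the protocol plans no calendar-period analysis. At RR 1.3 the extreme gap, 1995 against 2017, is 1.330 against 1.300.
- **That every control must stay cancer-free until 2017.** The rule concerns documented diagnoses. A woman who leaves the database is not excluded by a cancer recorded nowhere in it.

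What the reply does not remove is the mismatch between the declared nested design and the control rule, or the direction of the bias.

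**Conclusion.** The point holds as a minor one. Controls are selected on events after their index date, and odds ratios for harmful exposures are slightly overstated as relative risks: on average about 0.1-1.1% at RR 1.3 and 0.3-3.0% at RR 2. The size rests on assumed incidence of 63-350 per 100,000 per year, the document's prevalences of 20% and 33%, evenly spread index dates and a lasting effect. A rarer exposure would move the upper figure at RR 2 to about 4%; fading risk would lower every figure.

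The bias is largest for early index dates and older women, and the extension to 2017 lengthens the longest look-ahead from 16 to 23 years. It vanishes at RR 1, so type I error is unaffected, and the power statement stands.

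**What to change.** In both control definitions, require that a control has no invasive or in situ breast cancer recorded on or before the matched case's index date. State that women diagnosed later may serve as controls before their own diagnosis. Delete the condition that runs to the end of the data, and the amendment's sentence "Cases are therefore not eligible to act as controls in this study". The age, practice and observation-time matching can stay as it is. With controls sampled this way, the matched odds ratio estimates the rate ratio, so "crude and adjusted odds ratios (relative risks) with 95% confidence intervals" becomes accurate.

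The cost is a change of wording. The amendment already requests a full refresh with newly matched controls for 1995 to 2017, and no extra women are needed. Made after extraction, the change would need another one.

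If the existing rule is kept, say in the analysis and limitations sections that the odds ratio only approximates the rate ratio, with the direction of the error, and add a sensitivity analysis using risk-set sampled controls.

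### Exposure is read only from prescriptions dated inside the observation window, so women with a Mirena already in place can be analysed as unexposed; the cost is precision and a skew to early use, not a demonstrated failure of the power statement

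*Protocol*

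**What the plan says.** Under *Exposures, outcomes, covariates*, the Protocol treats a woman as exposed "if they have at least one prescription for a hormonal contraceptive or hormone replacement therapy preparation", with the prescription falling between start of follow-up and index date. *Data/statistical analysis outline methodology* sets the matching contrast: "hormone prescription vs no prescription within the observation period". That section also commits to a product-specific analysis of the intrauterine system: "for both, the risks associated with use of Mirena will be examined".

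The window can be short. *Study population* requires only one year in the database before the index date, and the 2017 amendment repeats this as 12 months of up-to-standard data.

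One sensitivity analysis varies the exposure definition, and it is stricter: "Sensitivity analyses will be performed restricting the definition of exposure to those with 2 or more prescriptions". No rule gives a device a duration of action or recognises one already in place.

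*Sample size and power calculations* states a minimum detectable relative risk "of <=1.5 for any subgroup with exposure prevalence of 1% or more". *Limitations* acknowledges that "prescriptions issued outside general practice will not always be recorded". It does not mention exposure that began before the window and continues through it.

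**The concern.** A prescription date is a good marker of current exposure when a product is re-prescribed every few months. It is a poor one for a device that is prescribed once and then releases hormone for years. If the window is shorter than the device's life, a woman can be exposed throughout it, up to the index date, with no prescription dated inside it. Unless she has some other hormone prescription in the window, the rule puts her in the reference group.

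Three things follow for the Mirena analyses:

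- Some exposed women are lost from the exposed group.
- In short windows the women who are captured were fitted recently, so the estimate describes mainly early use.
- The two-prescription sensitivity analysis removes a woman whose only record is one device prescription, so it makes the problem worse.

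The Background describes the risk with Mirena as unclear, and the amendment gives Mirena as one reason for extending the data. A null or imprecise Mirena result would be hard to interpret if it could reflect the coding rule.

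**Working it through.** **Inputs from the Protocol.** Power 80% and 95% confidence, read as two-sided 5%. At least 10,000 cases. The power section pairs these with 40,000 controls (4:1), while the design says 2 controls per case (2:1), so both are run. The amendment reports 33,000 cases and 66,000 controls from the extraction to 2010. The subgroup bound is 1.5 at prevalence of 1% or more.

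**Inputs not in the Protocol (assumptions).** Device life of 5 years, continuous use to the index date, and fitting times evenly spread. The share captured is s = min(1, window/5): 20% at 1 year, 40% at 2, 60% at 3, and 100% from 5 years. Capture is taken to be the same in cases and controls.

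**Formula.** The detectable OR solves log OR = 2.80 × √[1/(n₁p₁q₁) + 1/(n₀p₀q₀)], where q = 1 − p and p₁ = OR·p₀/(1 + p₀(OR − 1)).

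**Step 1: reproduce the stated bound.** With p₀ = 0.01, n₁ = 10,000 and n₀ = 20,000, try OR = 1.368:

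- p₁ = 0.01368/1.00368 = 0.01363.
- The variance is 0.00744 + 0.00505 = 0.01249, and its square root is 0.1118.
- 2.80 × 0.1118 = 0.313, and exp(0.313) = 1.37.

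At 4:1 the result is 1.33. A pooled two-proportion calculation gives 1.37 and 1.34. All are within 1.5. The overall bound of under 1.1 also reproduces: 1.07 to 1.08 at 33% prevalence and 1.08 to 1.09 at 20%.

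**Step 2: effect of missed devices on the odds ratio.** Take true prevalence 1%, true OR 1.5 and s = 0.2.

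- True case exposure is 0.015/1.005 = 0.014925.
- Recorded exposure is 0.002985 in cases and 0.002 in controls.
- The recorded OR is (0.002985/0.997015)/(0.002/0.998) = 1.494.

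**Step 3: effect on precision.** With *true* prevalence 1%, recorded prevalence is 0.01 × s. Detectable OR by the formula above:

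| Cases : controls | s = 100% | 60% | 40% | 20% | Capture at which 1.5 is lost |
|---|---|---|---|---|---|
| 10,000 : 40,000 | 1.33 | 1.43 | 1.53 | 1.76 | 44% |
| 10,000 : 20,000 | 1.37 | 1.48 | 1.60 | 1.89 | 56% |
| 33,000 : 66,000 | 1.20 | 1.26 | 1.32 | 1.46 | 17% |

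The pooled calculation puts the break-even at 48%, 58% and 18%. The ranges are therefore about 44–58% at 10,000 cases and 17–18% at 33,000.

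**Step 4: what those thresholds mean in years.** With a 5-year life and one common window length, 44–58% corresponds to 0.44 × 5 = 2.2 to 0.58 × 5 = 2.9 years. For 33,000 cases, 0.18 × 5 = 0.9 years, which is below the 12-month minimum. Under these assumptions the bound would therefore survive there even if every window were the shortest allowed, before any further loss from devices fitted outside the practice.

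**Step 5: if 1% means recorded prevalence.** For capture of 20% to 100% (true prevalence 5% to 1%), 10,000 cases detect a true OR of 1.34 to 1.39 by the pooled calculation. The bound holds throughout.

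**The case against.** A reader might infer that the subgroup detectability claim fails for devices. The documents do not support that. The bound is conditional on prevalence of 1% or more, and the power section's own prevalences are of prescribing, so recorded prevalence is the natural reading. On that reading the bound holds. A subgroup that falls below 1% because devices are missed lies outside the statement and does not contradict it. On the other reading, failure needs low capture, and the documents give neither capture, nor device prevalence, nor the distribution of windows. One year is the minimum window, not the typical one. If windows were evenly spread from 1 to 5 years, mean capture would be 3/5 = 60% and the detectable OR about 1.43 to 1.49 with 10,000 cases. The contraceptive analyses, limited to ages 20–50, will have fewer cases, but the number is not given. A shortage of cases there would be a separate reason for losing the bound: 5,000 cases at 2:1 give 1.54 with full capture.

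A reader might also infer serious bias from device users sitting in the reference group. Step 2 shows the effect is negligible at low prevalence, and exact matching of windows within sets gives no evident reason for capture to differ between cases and controls.

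Other points in the plan's favour also stand. Devices fitted outside the practice are largely covered by the stated limitation on prescriptions issued elsewhere. Mirena appears in the Background, the methods and the amendment, but not in the specific aims. Implants are never named and enter only as hormonal or progestagen-only contraception.

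It can be argued that device rules and code lists belong in an analysis plan. That is fair for the code lists. But the Protocol fixes both the exposure rule and its reference group, and as written they classify a current device user as unexposed.

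**Conclusion.** The point holds as a defect in the exposure definition for long-acting devices. Read as written, the rule assigns current Mirena users fitted before the window, with no other in-window hormone prescription, to the reference group. The only sensitivity analysis on the definition moves further in the wrong direction.

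The consequence is fewer recorded exposed women, and hence less precision, together with a tilt towards early use when windows are short. If the 5-year assumption is near the truth, a set with a 12-month window captures about one current user in five, and a set with five years or more captures all of them. How much this matters overall depends on the distribution of windows, which the documents do not give. The power statement stands as written, and material bias in the odds ratio is not shown.

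**What to change.** For Mirena and any other long-acting device, define exposure as device in place during the observation window. Accept as evidence a prescription, or a Read-coded fitting, check or removal, dated inside the window. Apply the rule identically to cases and controls, and use in-window evidence only, because controls may have more record before the window than their case. Exempt devices from the two-prescription rule.

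Keep all matched sets in the main Mirena estimate. Add a sensitivity analysis restricted to sets whose window is at least the assumed device life, and state that life. Making the restricted sets primary would be a debatable trade, since it discards users already captured in shorter windows and recovers none of those missed.

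The cost is one further code list, provided that clinical codes are in the extract or can be included in the refresh requested by the amendment, and lower precision in the restricted analysis. Women whose device left no in-window record of any kind will still be missed; *Limitations* should say so.
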